
### Data collection plan

Baseline, assessment, and collection results will be documented on a paper Case Report Form (CRF). Data collection will be conducted by trained researchers who will receive instructions on how to perform the assessments. The two MRI scans before and after treatment will be conducted at the Yunying Medical Imaging Diagnosis Center in Xi’an, China.

### Data management

The data collected will be kept strictly confidential. Paper-based behavioral data will be periodically entered into the computer and converted into electronic data. Magnetic resonance data will also be promptly stored in the departmental database. Principal Investigators have access to the full dataset. Regular Review of Accumulated Data by the Ethics Committee of Xijing Hospital.

### Data access

Any data required to support the protocol can be supplied on request.

### Dissemination policy: reproducible research

Upon reasonable request, corresponding authors may provide the datasets used and analyzed in the current study, with the exception that participants' personal information will not be disclosed.

### Data monitoring: formal committee

To ensure the blinding, safety, and validity of the study, a Data Monitoring Committee (DMC) was established at the hospital. The committee consists of independent ethical, statistical, and clinical physicians and is independent of sponsors and competing interests. Any adverse reactions will be promptly reported to the DMC and relevant regulatory agencies.

### Harms

Common adverse reactions include dizziness, headache, and tingling of the scalp. The main potential adverse reactions include seizures. As a result, all researchers involved in the study will receive training related to seizures before enrolling participants to ensure their safety. Any adverse reactions will be recorded in a paper CRF and reported immediately to the DMC and relevant regulatory agencies.

### Auditing

The Ethics Committee will provide continuous regulatory oversight. The Ethics Committee will convene annually to ensure that researchers adhere to the study protocol, procedures, and regulations and that the research data obtained are objective, truthful, and integral.

### Statistical analysis

All data were analyzed based on the intention-to-treat principle, aiming to maintain the true state of the intervention as accurately as possible. Multiple imputations will be used to handle missing data.

#### Data analysis

Data analysis before intervention

The chi-square or Kruskal–Wallis tests will be used to examine all sociodemographic information, as well as the results of the pretreatment scale. Baseline information between groups will be analyzed using either a paired t-test or a rank sum test. All tests are two-sided tests, with a significance level of *p* ≤ 0.05.

2.Overall clinical scale data analysis

The ODQ scale, MADRS scale, Beck Scale for Suicide Ideation-Chinese Version (BSI-CV), and other scores will be examined during the treatment and follow-up period using repeated measures analysis of variance to examine differences between groups before and after the intervention.

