### Trial design

This trial is a randomized, controlled, double-blind, parallel-group, superiority, and single-center study in which eligible participants were randomly assigned to one of two groups: (1) fMRI-rTMS or (2) sham stimulation. Both groups received a combination of antidepressant medications. The study aims to compare the improvement of emotional blunting and depressive symptoms.

The Oxford Depression Questionnaire (ODQ) scores compared between the two groups at various time points served as the primary outcome measure [5]. Other depressive symptoms, such as the Montgomery and Asberg Rating Scale (MADRS) scale following the intervention, will be examined as the secondary outcome [17]. The evaluation time will be at the treatment baseline, after the 7th day of treatment, after the 15th day of treatment, and at the end of the 2nd, 4th, and 8th weekends after the treatment to further clarify the onset time and maintenance of fMRI-rTMS. In addition, structural and functional magnetic resonance imaging (MRI) is performed on the subjects using magnetic resonance imaging, combined with the precise targeted therapeutic effect of fMRI-rTMS on the functional connection of the mPFC-amygdala, to reverse verify the role of the mPFC and amygdala in the neural mechanism of depressive emotional blunting. This trial will follow the SPIRIT guidelines [18], and the SPIRIT checklist is shown in Additional file 1. The detailed flow chart is shown in Fig. 1. This study has been approved by the Ethical Committee of Xijing Hospital, Xian, China (XJLL-KY20222175) and is registered with the ClinicalTrials.gov database (NCT05555940).

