### Sample size

By reviewing the literature and using the primary outcome ODQ scores, the pre-set ODQ score of the fMRI-rTMS group was 63 ± 23 [19], while the ODQ score in the sham stimulation group was 80 ± 18 [20]. The significance level for the test was set at *α* = 0.05, the power at *β* = 0.1, with a confidence level of 0.9, and the sample size was determined to be 66 cases using PASS 11 software. Because of the potential loss of experimental data or subject withdrawal from the trial, the sample size was increased by 20%. To ensure the balance of the two groups, 80 cases were finally included in the trial.

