## Outcome measures

### Primary outcome measure

Our primary outcome will be the changes in ODQ scores [5]. It is a relatively new emotional blunting assessment tool for the self-rating scale, which consists of three parts and 26 questions, focusing on the patient's emotional experience over the previous week. The first part comprised 12 questions aimed at evaluating the subjects' current experience of emotional blunting. The second part consists of 8 questions designed to compare the patient's current state with their normal state before experiencing depression. The third part included 6 questions to gauge the extent to which patients believed their emotional blunting was linked to antidepressants, as well as whether these issues affected their treatment adherence. Each question is graded on a 5-point scale, ranging from 1 (disagree) to 5 (agree). The score and total score of each dimension were summarized (total score range: 26–130). The higher the value of ODQ is, the greater the degree of emotional blunting. The Chinese version of the ODQ has been validated to have good reliability [21].

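### The repeated-measures ANOVA for ODQ makes no adjustment for the baseline score that the trial collects, so precision is left unused and, on some readings, the stated effect is not what is estimated

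*Protocol article*

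**What the plan says.** The Data analysis section of the protocol article gives one efficacy model for ODQ, MADRS, BSI-CV and the other scales. The sentence first says that "scores will be examined during the treatment and follow-up period" and ends with "using repeated measures analysis of variance to examine differences between groups before and after the intervention". It names no covariate, and it does not say whether the group effect, the group-by-time interaction or a contrast at one visit is tested.

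The Primary outcome measure section states: "Our primary outcome will be the changes in ODQ scores". The Trial design section says that ODQ "scores compared between the two groups at various time points served as the primary outcome measure", and sets six assessments: "The evaluation time will be at the treatment baseline, after the 7th day of treatment, after the 15th day of treatment", then weeks 2, 4 and 8 after treatment. The inclusion criteria require a minimum baseline ODQ total, so every participant has a baseline value.

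The Sample size section is a comparison of two means: "the pre-set ODQ score of the fMRI-rTMS group was 63 ± 23", against 80 ± 18 under sham. On missing data, the Statistical analysis section says: "Multiple imputations will be used to handle missing data".

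**The concern.** In a randomised trial the two arms have the same expected score before treatment. A model that makes baseline one more outcome level, and tests the group effect averaged over all levels, includes a visit at which the true difference is zero. The group-by-time interaction avoids this, but it asks only whether the two profiles differ in shape and gives no single treatment difference. If the model uses post-baseline visits alone, baseline drops out of the analysis.

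On none of these readings is baseline ODQ a covariate. The trial was sized on a 17-point between-group difference. At stake are whether the analysis estimates such a difference and how precisely. This matters most if the effect is not constant over visits. The Trial design section gives onset and maintenance of the effect as the reason for the repeated assessments.

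**Working it through.** **Inputs from the protocol article.** Means 63 and 80, SDs 23 and 18, two-sided alpha 0.05, power 0.90, 1:1 allocation, 66 participants before dropout and 80 after, baseline plus five later visits.

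**Assumptions (not in the article).** Common SD at every visit; the same correlation ρ between any two visits (compound symmetry), shown from 0.3 to 0.7; complete data; the effect profiles below.

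**1. The article's own figure.** Difference 80 − 63 = 17. SD = √((23² + 18²)/2) = √426.5 = 20.65. The unequal-variance t-test has power 0.899 at 32 per arm and 0.908 at 33 per arm, so 33 per arm, or 66 in total, reproduces the stated number. It rests on an unadjusted comparison of two means, not on a repeated-measures model.

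**2. Size of the averaged effect.** With baseline as one of six levels:
- constant 17 points after baseline: 17 × 5/6 = 14.17
- build-up and waning (0, 8.5, 17, 12.75, 8.5, 4.25): 51/6 = 8.50, against 51/5 = 10.20 over the five post-baseline visits

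**3. Standard errors.** Each is 20.65 × √(2/33) × √f = 5.08 × √f, with
- main effect over six levels: f = (1 + 5ρ)/6
- mean of five post-baseline visits, unadjusted: f = (1 + 4ρ)/5
- the same, adjusted for baseline: f = (1 + 4ρ)/5 − ρ²

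At ρ = 0.5, f is 0.583, 0.600 and 0.350, giving SEs of 3.88, 3.94 and 3.01.

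The group-by-time test has 5 and 5 × 64 = 320 degrees of freedom and noncentrality (33/2) × Σ(δₜ − mean δ)² / (426.5 × (1 − ρ)). For the constant effect at ρ = 0.5 this is 16.5 × 240.83/213.25 = 18.63.

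**4. Power at 33 per arm.**

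| Profile and analysis | Effect | ρ = 0.3 | 0.5 | 0.6 | 0.7 |
|---|---|---|---|---|---|
| Constant: main effect, six levels | 14.17 | 0.989 | 0.949 | 0.919 | 0.887 |
| Constant: group-by-time | – | 0.809 | 0.932 | 0.975 | 0.996 |
| Constant: post-baseline mean, unadjusted | 17 | 0.999 | 0.989 | 0.979 | 0.965 |
| Constant: post-baseline mean, adjusted | 17 | >0.999 | >0.999 | >0.999 | >0.999 |
| Waning: main effect, six levels | 8.50 | 0.723 | 0.578 | 0.523 | 0.477 |
| Waning: group-by-time | – | 0.668 | 0.830 | 0.913 | 0.975 |
| Waning: post-baseline mean, unadjusted | 10.20 | 0.846 | 0.723 | 0.669 | 0.620 |
| Waning: post-baseline mean, adjusted | 10.20 | 0.916 | 0.916 | 0.937 | 0.967 |

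**5. Precision at one visit.** Relative variances are 1 for the raw score, 2(1 − ρ) for change and 1 − ρ² for the adjusted score. Adjustment therefore saves ρ² against raw and (1 − ρ)/2 against change:
- ρ = 0.5: 25% and 25%
- ρ = 0.6: 36% and 20%
- ρ = 0.3: 9% and 35%
- ρ = 0.7: 49% and 15%

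Power for 17 points at one visit, adjusted, is 0.932 / 0.967 / 0.984 / 0.996 for ρ = 0.3 / 0.5 / 0.6 / 0.7, against 0.909 for the raw score.

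**The case against.** Much of the case for the plan stands.

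- **Dilution is conditional.** A reader might infer that the plan certainly dilutes the effect. That needs baseline to be a level and the main effect to be the deciding test. The reference to the treatment and follow-up period allows a post-baseline-only model. If baseline is a level, group-by-time is the usual term for a before-and-after comparison; it is not diluted and it already uses baseline.
- **Power.** A reader might infer that the trial is underpowered. For a constant 17-point effect it is not: even the main effect over six levels has power 0.94 or more at 40 per arm for ρ up to 0.7.
- **Sphericity.** In simulations under no treatment effect, with correlation decaying over time, the uncorrected group-by-time test rejected in about 8 to 9% of trials. With a Greenhouse–Geisser correction the rate was about 5%. The article does not say that the test will be uncorrected, so inflated type I error cannot be charged to it.
- **Missing data.** Multiple imputation supplies the complete rows that the model needs, and it is a legitimate method when data are missing at random.
- **Size of the gain.** The primary outcome is a change, so the fairer comparison is with change scores, where the saving is 20 to 25% at ρ of 0.5 to 0.6. The minimum ODQ score at entry restricts the baseline range and may lower ρ.
- **Scope.** A condensed article may leave the covariate, the tested term and the primary visit to an analysis plan that is not shown.

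The scope argument does not remove the point. The article does more than stay silent on detail: it names the model. At every correlation and for both profiles in the table, adjusting the post-baseline mean for baseline gives a smaller standard error and higher power than leaving it unadjusted.

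**Conclusion.** The point holds as a matter of efficiency and of what is estimated, not of validity. Repeated-measures ANOVA is a valid choice in a randomised trial, but as stated it leaves the baseline ODQ score unused as a covariate.

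The cost depends on which reading the sponsor intends:
- **Main effect, baseline included:** 17 points become 14.2 if the effect is constant, and 8.5 under the assumed waning profile, where power falls to 0.52–0.58 at ρ of 0.5 to 0.6.
- **Group-by-time:** no dilution, and power of 0.83–0.91 under the same waning profile, but no estimate of the difference on which the trial was sized.
- **Post-baseline only, unadjusted:** no dilution, but power of 0.67–0.72 against 0.92–0.94 with adjustment.

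The correlations, compound symmetry, common SD, complete data and effect profiles are assumptions; the article gives none of them. It also names no time point for the 17 points, so it cannot be said that the plan misses a specific day-15 target.

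**What to change.** For ODQ, and likewise for the other continuous scales, replace the repeated-measures ANOVA with a mixed model (or ANCOVA) on the post-baseline visits. The terms are treatment, visit, treatment-by-visit and baseline score as covariate. Before unblinding, the sponsor should name the one treatment contrast that decides the primary comparison, for example end of treatment or the average over post-baseline visits. The mixed model uses all observed post-baseline scores, so multiple imputation can be kept as a sensitivity analysis. If an analysis plan already contains this, the article's sentence should be brought into line with it.

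The cost is a change of wording. No new data, visits or patients are needed.

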#### MRI data analysis

SPM and other tools will be used to statistically evaluate the magnetic resonance data. The differences between the experimental and control groups as well as changes in imaging indicators such as functional connectivity, low-frequency amplitude, and local consistency will be investigated using the double-sample *t*-test.

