**Methods:**

This study is a randomized, controlled, double-blind, and single-center clinical trial in which 80 eligible depressed patients with emotional blunting will be randomly assigned to two groups: a functional magnetic resonance imaging-guided personalized rTMS (fMRI-rTMS) group and a control group. Individuals in the fMRI-rTMS group (*n* = 40) will receive high-frequency rTMS (10 Hz, 120% MT). The main target of stimulation will be the area most relevant to the functional connectivity of the right medial prefrontal cortex (mPFC) and amygdala. The control group (*n* = 40) will receive sham stimulation, with a coil flipped to 90 degrees relative to the vertical scalp. All patients will receive 15 consecutive days of treatment, with each session lasting half an hour per day, followed by 8 weeks of follow-up. The primary outcome is the comparison of Oxford Depression Questionnaire (ODQ) scores between these two groups at different time points. The secondary outcomes include evaluating other clinical scales and assessing the differences in brain imaging changes between the two groups before and after treatment.

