A meta-analysis of major depressive disorder (MDD) found reduced coupling between the medial prefrontal cortex (mPFC) and the amygdala [8]. Both the increase and decrease in emotion activate the prefrontal cortex, and the downregulation of emotion is related to more right-lateralized activity [9]. Limbic structures, such as the amygdala, are less responsive to emotional stimuli, and subjects experience emotional blunting [10]. Using rTMS to stimulate the right mPFC, researchers found that high-frequency (20 Hz) rTMS enhanced the functional connection between the right amygdala and mPFC, while low-frequency (1 Hz) rTMS weakened the functional connection [11]. Right-sided high-frequency stimulation of the dorsolateral prefrontal cortex attenuates the processing of negatively valenced emotional stimuli in the right amygdala of healthy women [12].

In clinical practice, the transcranial magnetic stimulation site is typically set 5–6 cm in front of the motor cortex. However, this method is inaccurate [13]. According to increasing amounts of evidence, personalized interventions enhance the efficacy of transcranial magnetic stimulation therapy [14–16]. Therefore, we hypothesized that compared with the sham stimulation group, stimulating the most relevant functional connection between the right mPFC and amygdala with fMRI-rTMS could increase prefrontal cortex activity and decrease amygdala activity, thereby alleviating symptoms of emotional blunting in patients with depression.

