## Methods/design

### Objective

The primary objective is to explore the efficacy and safety of fMRI-rTMS precise stimulation of right mPFC-amygdala individualized targets in the treatment of depression patients with emotional blunting.The secondary objective is to analyze the neuroimaging mechanism that may be related to depressive emotional blunting symptoms by comparing the differences in imaging changes before and after fMRI-rTMS treatment in combination with clinical efficacy and to verify the mechanism of mPFC-amygdala functional connection in depressive emotional blunting symptoms.

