### Secondary outcome measure

Alterations in baseline scores on the seventeen-item Hamilton Depression Rating Scale, Montgomery-Asberg Depression Rating Scale, and other clinical scales will be used as secondary outcome measures both during treatment and at each follow-up point. The specific evaluation times were at baseline, at the end of treatment on day 7, at the end of treatment on day 15, 2 weeks after treatment, four weeks after treatment, and eight weeks after treatment.Seventeen-item Hamilton Depression Rating Scale (HAMD-17). HAMD is a widely used clinical tool for assessing the severity of depression [22]. The higher the total score, the worse the symptoms. The Chinese version of the 17-item Hamilton Depression Rating Scale demonstrated excellent interrater reliability, good item-total score correlations, and satisfactory internal reliability [23].Montgomery-Asberg Depression Rating Scale (MADRS). Each item is divided into 6 levels according to the identity level, with a score of 0–6 points. The total score of patients is 0–60. The higher the score of patients, the more severe the depression. The Chinese version exhibits high reliability, validity, and internal consistency. It is more sensitive in assessing efficacy than the HAMD [24].The Chinese Version of the Beck Scale for Suicide Ideation (BSI-CV). It is primarily used to identify individuals with suicidal tendencies and to assess the severity of suicidal thoughts. The assessment consists of 19 items, with each item offering 3 scoring options (0–2 points, respectively), resulting in a total score range of 0–38 points. A higher score indicates an elevated risk of suicide. The Chinese version exhibited high internal reliability and strong item-total correlations [25].Beck Depression Inventory (BDI). The self-rating scale is used to assess the severity of depressive symptoms. The assessment consists of 21 items, each divided into 4 levels of scores ranging from 0 to 3. The total score of the scale is the sum of the scores from all 21 entries. A higher total score indicates more severe symptoms of depression. The Chinese version demonstrates good reliability and validity in patients with depression [26].Insomnia Severity Index (ISI). The Chinese version of the ISI questionnaire has good reliability and validity in evaluating the perceived severity of insomnia [27]. The scale consists of 7 items, each scored from 0 to 3, resulting in a total score ranging from 0 to 28, with higher scores indicating poorer sleep quality.Clinical Global Impression (CGI). During each visit, the clinician evaluates the patient's overall condition, considering the severity of the illness, the patient's distress level, any other impairments, and the impact of the illness on functioning [28].Perceived Deficit Questionnaire for Depression (PDQ-D). The PDQ-D provides a subjective assessment of cognitive dysfunction. The Chinese version of the PDQ-D has been determined to be psychometrically valid for assessing subjective cognitive dysfunction in patients with depression [29]. The questionnaire comprises 20 questions, each scored from 0 to 4 points, with a total score ranging from 0 to 80 points. The higher the score, the more severe the cognitive impairment.The frequency and seriousness of adverse reactions, the occurrence of adverse events connected to the treatment, and the frequency of dropouts as a result of adverse reactions.Differences in brain imaging before and after therapy. Each patient underwent an MRI before and after treatment to determine the blood oxygen levels in each brain region. From this information, the functional connectivity between brain regions can be statistically determined, and the differences between the functional connectivity before and after treatment are then compared.

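### The imaging plan names one unadjusted two-sample t-test for both group differences and changes, and does not fix which contrast is tested; a between-arm comparison adjusted for the pre-treatment scan would settle this and be more precise.

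*Protocol article*

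**What the plan says.** All references are to the protocol article.

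- **MRI data analysis.** One sentence sets the test for two items. The first is "The differences between the experimental and control groups". The second follows directly: "as well as changes in imaging indicators such as functional connectivity, low-frequency amplitude, and local consistency will be investigated using the double-sample" t-test. No paired, baseline-adjusted or group-by-time test is named for imaging.
- **Abstract, Methods.** The imaging outcome is given as "assessing the differences in brain imaging changes between the two groups before and after treatment", which is a between-arm contrast of changes.
- **Objective.** The mechanism objective is to be met by "comparing the differences in imaging changes before and after fMRI-rTMS treatment in combination with clinical efficacy". Sham is not mentioned.
- **Secondary outcome measure.** Each patient has one scan before and one after treatment, and "the differences between the functional connectivity before and after treatment are then compared". No comparator is named.
- **Assignment of interventions.** Patients are randomized 1:1, with 40 per arm.
- **Data analysis.** Tests are two-sided at 0.05. This section also names a paired t-test for comparing the two independent groups at baseline.

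**The concern.** Two scans on the same patient are correlated, and an independent-samples test makes use of that only if it is applied to a within-patient quantity such as the change score. The MRI section lists changes as a second item next to group differences and gives both the same test. It can therefore be read as pre versus post within an arm, as change scores between arms, or as post-treatment values between arms. These differ in meaning and in precision. The other sections do not settle the matter, because the abstract points one way and the Objective and Secondary outcome measure sections are worded another way. The paired test named for independent groups at baseline is a further reason not to rely on the reader to supply the right structure.

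At stake is the secondary objective of verifying the role of mPFC-amygdala connectivity. A conclusion built on within-arm before-after results would not use the randomized control. A between-arm test that leaves out the baseline scan as a covariate gives up precision that the collected data already offer.

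**Working it through.** **Plan's own figures.** The protocol gives no sizing or precision figure for imaging, so there is none to reproduce. Its only sizing figure, 66 for the ODQ, does reproduce. The difference is 80 − 63 = 17 and the SD is √((23² + 18²)/2) = 20.65. The unequal-variance t-test has power 0.899 at 32 per arm and 0.908 at 33 per arm, and 2 × 33 = 66. Nothing below depends on it.

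**Inputs.** n = 40 per arm and two-sided 0.05, from the protocol. The pre-post correlation r is not given, so r = 0.3 to 0.7 is assumed. Pre and post variances σ² are taken as equal.

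**Reading A: pre versus post within an arm, treated as independent.** The variance used is 2σ²/n and the correct paired variance is 2σ²(1 − r)/n. The SE ratio is 1/√(1 − r). Simulation at 40 per arm (20,000 trials per setting) gives the error rates and the power for a 0.5 SD shift.

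| r | SE ratio | Type I error, independent | Power, independent | Power, paired |
|---|---|---|---|---|
| 0.3 | 1/√0.7 = 1.20 | 2.1% | 62% | 74% |
| 0.5 | 1/√0.5 = 1.41 | 0.7% | 64% | 87% |
| 0.7 | 1/√0.3 = 1.83 | 0.1% | 66% | 98% |

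The paired test stays at about 5% under the null. The error is thus conservative: it loses power and does not create false positives.

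**Reading B: change scores, or post-treatment values, between arms.** Both are valid. Simulated type I error for the change-score test is 4.9% to 5.1%. Per-patient variances are:

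- change score: 2σ²(1 − r)
- post value only: σ²
- post value adjusted for baseline (ANCOVA): σ²(1 − r²)

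The ratio of ANCOVA to change score is (1 − r²)/(2(1 − r)) = (1 + r)/2. The ratio of ANCOVA to post-only is 1 − r².

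| r | ANCOVA / change score | ANCOVA / post only |
|---|---|---|
| 0.3 | 0.65 | 0.91 |
| 0.5 | 0.75 | 0.75 |
| 0.7 | 0.85 | 0.51 |

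In sample-size terms, a change-score test with 40 per arm has the precision of an adjusted analysis with 40 × 0.65 = 26, 40 × 0.75 = 30 or 40 × 0.85 = 34 per arm. The small loss of degrees of freedom for the covariate is ignored. Adjustment has the lower variance than either alternative at every r in the range.

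**The case against.** The strongest reply is that the plan is already sound. The abstract says what is compared, a two-sample t-test on per-patient changes does exactly that, and it respects the pairing. This largely stands. A reader might infer that the analysis ignores pairing, but the documents do not establish that; they only fail to rule it out. What remains is that two other sections word the comparison as before versus after, and that even the valid reading is less precise than it need be.

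A reader might also infer that regression to the mean biases the mechanism result, because "The main target of stimulation will be the area most relevant to the functional connectivity of the right medial prefrontal cortex (mPFC) and amygdala". The documents do not support this as a stated defect. They do not say that the target is the most connected site on the baseline scan, and no section limits the imaging outcome to the target. If the target were a baseline maximum (assumed: 5, 20 or 100 independent candidate sites, reliability 0.3 to 0.7), simulation with no treatment effect gives a within-arm shift of −0.35 to −1.75 SD, and a paired within-arm test rejects in 84% to 100% of trials. The between-arm difference in change, however, is −0.010 to +0.007 SD, with rejection in 5.1% to 5.9%. The effect cancels between randomized arms if targets are chosen alike. It is a reason to prefer the between-arm contrast and no more.

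Lastly, a reader might infer that the hypothesis cannot be refuted, because the Background states "Limbic structures, such as the amygdala, are less responsive to emotional stimuli, and subjects experience emotional blunting" and then expects that stimulation "could increase prefrontal cortex activity and decrease amygdala activity, thereby alleviating symptoms of emotional blunting". The tension is real, but it is a separate background matter. Responsiveness to stimuli and activity are not clearly the same quantity, a null between-arm result would still count against the hypothesis, and none of this makes the t-test wrong. A single named imaging endpoint and exploratory labels may sit in an analysis plan that is not shown.

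**Conclusion.** The point holds as a matter of an unfixed contrast and avoidable imprecision. The MRI section assigns one unadjusted independent-samples test to paired data without saying what it is applied to, and the sections that describe the imaging comparison do not agree. Under the within-arm reading the SE is 1.2 to 1.8 times too large and the test is conservative. Under the between-arm readings it is valid, but adjustment for the pre-treatment scan would cut the variance to 0.65 to 0.85 of the change-score variance, or 0.51 to 0.91 of the post-only variance. These figures rest on an assumed r of 0.3 to 0.7 and equal variances; the protocol gives neither. The reach is limited to the secondary mechanistic objective. The ODQ primary analysis and the sample size are unaffected.

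**What to change.** In MRI data analysis, state that each imaging indicator is tested as the between-arm difference in post-treatment value adjusted for the pre-treatment value (ANCOVA), at the two-sided 0.05 level already set. Carry the same contrast into the Objective and Secondary outcome measure sections, naming sham as the comparator. Base the mechanism conclusion on that contrast, and report within-arm before-after results descriptively with paired tests. State whether targets are selected in the same way in both arms, since protection against any regression to the mean at the target depends on it. If the imaging software cannot carry a baseline covariate for some indicator, a two-sample test on per-patient change scores is a valid fallback at the precision cost shown.

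The cost is wording only: the same two scans per patient are used and no data are added. The change should be made before unblinding.

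### The imaging plan names only a two-sample t-test for group differences and for changes, without saying what enters it; a baseline-adjusted comparison of the arms would settle the reading and be at least as precise

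*Protocol article*

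**What the plan says.** The section on MRI data analysis gives one sentence on testing. Its subject has two parts, "The differences between the experimental and control groups as well as changes in imaging indicators", and both fall under the same two-sample t-test: "changes in imaging indicators such as functional connectivity, low-frequency amplitude, and local consistency will be investigated using the double-sample" t-test. It names no paired test, repeated-measures model or baseline adjustment for imaging.

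The design yields two scans per patient: "Each patient underwent an MRI before and after treatment to determine the blood oxygen levels in each brain region" (Secondary outcome measure).

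The imaging question is worded in three ways elsewhere:
- Abstract, Methods: "assessing the differences in brain imaging changes between the two groups before and after treatment". This is a change compared between arms.
- Objective: "comparing the differences in imaging changes before and after fMRI-rTMS treatment". The sham arm is not mentioned.
- Secondary outcome measure: "the differences between the functional connectivity before and after treatment are then compared". The groups are not mentioned.

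For the clinical scales, the Data analysis section names repeated measures analysis of variance, so a within-patient method is stated there but not for imaging.

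**The concern.** The two scans of a patient are correlated. A two-sample t-test assumes independent samples, so it suits a comparison of the arms but not a comparison of a patient's before scan with the same patient's after scan. One test is assigned to both group differences and changes, so the text does not settle what the two samples are. Three analyses fit it:

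1. per-patient change compared between arms;
2. before against after scans, entered as independent samples;
3. after-scan values compared between arms, with the before scan unused.

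They differ in the quantity estimated, in precision or in both, and the choice could be made after the data are seen. The secondary objective, to verify the role of the mPFC-amygdala connection, rests on these tests.

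The Data analysis section adds some doubt about how tests are matched to comparisons: "Baseline information between groups will be analyzed using either a paired t-test or a rank sum test". The arms are independent, so a paired test does not fit that comparison.

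**Working it through.** The protocol gives no numerical figure for the imaging test, so there is none to reproduce. Its sample size calculation concerns the ODQ and plays no part here.

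**Inputs**
- n = 40 per arm (Assignment of interventions).
- Two-sided tests at 0.05 (Data analysis: "All tests are two-sided tests, with a significance level of" 0.05).
- Scan-rescan correlation r: not given. Assumed 0.3, 0.5 and 0.7.
- Equal variance at both scans, the same r in both arms, complete data: assumed. Standard errors are in units of the single-scan SD.

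**Step 1. Between-arm comparisons**
- After-scan values: SE = sqrt(2/n) = sqrt(2/40) = 0.224.
- Per-patient change: SE = sqrt(2 × 2(1-r)/n) = sqrt((1-r)/10).
- After-scan value adjusted for before-scan value: SE ≈ sqrt(2(1-r²)/n) = sqrt((1-r²)/20).

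The ratio of adjusted to change-score SE is therefore sqrt((1+r)/2). The ratio of adjusted to after-scan SE is sqrt(1-r²).

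| r | SE, after-scan | SE, change | SE, adjusted | adjusted / change | adjusted / after-scan |
|---|---|---|---|---|---|
| 0.3 | 0.224 | 0.265 | 0.213 | 0.81 | 0.95 |
| 0.5 | 0.224 | 0.224 | 0.194 | 0.87 | 0.87 |
| 0.7 | 0.224 | 0.173 | 0.160 | 0.92 | 0.71 |

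Both ratios stay below 1 for any r strictly between 0 and 1. The adjusted model uses 3 parameters instead of 2, so with 80 patients the residual degrees of freedom go from 78 to 77.

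**Step 2. Validity of the change-score reading**

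In 20,000 simulated trials per value of r, with 40 per arm and no true effect, a two-sample t-test on change scores between arms rejected in 0.047 to 0.051 of trials for r from 0 to 0.8. On this reading there is no error.

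**Step 3. Before and after scans of one arm as independent samples**

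Paired SE = sqrt(2(1-r)/n); unpaired SE = sqrt(2/n); ratio = 1/sqrt(1-r). Rejection rates come from 20,000 simulations with n = 40. The power columns assume a true within-arm change of 0.5 SD.

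| r | SE ratio, unpaired / paired | type I error, unpaired | type I error, paired | power, unpaired | power, paired |
|---|---|---|---|---|---|
| 0.3 | 1.20 | 0.020 | 0.050 | 0.62 | 0.75 |
| 0.5 | 1.41 | 0.007 | 0.048 | 0.64 | 0.87 |
| 0.7 | 1.83 | 0.001 | 0.050 | 0.67 | 0.98 |

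With positive r the unpaired test errs on the conservative side: it misses real changes and does not create false ones. These figures apply only if that test were actually run.

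**The case against.** A reader might infer that the plan treats the two scans of a patient as independent and so reports wrong standard errors. The document does not establish that. The only two samples the MRI sentence names are the experimental and control groups; it never says that the samples are the before and after scans. The changes it mentions can equally be the variable compared between those groups, and the abstract's wording supports this. The outcome section can also be read this way, since what it says is compared are the differences. On that reading the stated test is valid, and the figures in Step 3 do not apply. This part of the objection stands.

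It can also be said that comparing after-scan values alone conflicts with the abstract and, under randomisation, would still be unbiased. That is right: the cost of ignoring the before scan is precision, plus whatever chance baseline imbalance remains in the estimate.

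A further inference, that the plan is deficient for not adjusting for head motion, is not supported either. Such covariates are detail that a condensed article commonly leaves to the full plan.

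The objection does not show that the sentence settles the analysis. The abstract points to the valid use, but the section that assigns the test does not state it, and two other sections describe the comparison without naming both groups. Nor does the objection remove the precision gain over a t-test on change scores.

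**Conclusion.** The point holds as an ambiguous test assignment for which a better method is available, not as a proven wrong test. The stated two-sample t-test is valid for per-patient change compared between arms. The wording also admits an unpaired test of paired scans, with a standard error 1.20 to 1.83 times too large for assumed r of 0.3 to 0.7, and a comparison that discards the before scan.

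Even on the valid reading, adjusting for the before scan cuts the standard error by about 19%, 13% or 8% at r = 0.3, 0.5 or 0.7. Compared with after-scan values alone, the cut is about 5%, 13% or 29%. These sizes rest on the assumed correlations, equal variances and complete data. The outcome is secondary and mechanistic, and the primary ODQ analysis is not affected.

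**What to change.** In the MRI data analysis section, replace the single t-test sentence with two statements:

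- For each imaging index, the arms are compared with a linear model of the after-scan value on arm and before-scan value, and the arm coefficient is reported with its confidence interval. Where an analysis cannot take the before-scan value as a covariate, a two-sample t-test on one change value per patient is a valid fallback.
- Any before-after statement within an arm uses a paired test and is labelled descriptive.

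Use the abstract's definition, change compared between the two groups, in the Objective and Secondary outcome measure sections as well. At the same time, replace the paired t-test named for the between-group baseline comparison with a test for independent samples.

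The cost is about one degree of freedom per model and a wording change. Both scans are already planned, so no new data are needed.
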